## Project

### THEORETICAL-CONCEPTUAL CONTEXT

#### INTRODUCTION. TENSION-TYPE HEADACHE.

##### DEFINITION

Tension-type headache is a type of primary headache that was first described in 1988 by the International Headache Society. Several types of headaches with common clinical features are included within the term tension headache. The latest edition of the 2013 International Classification of Headaches (ICHD-III), includes the following main characteristics for this type of headache: pain in the cephalic region typically bilateral, of oppressive quality, with mild to moderate intensity, with a duration ranging from minutes to days. The pain does not worsen with physical activity and is not associated with nausea, photophobia, or phonophobia (but may occasionally be present).

If the duration of the episodes and their frequency are taken into account, four subtypes are established as shown in the following classification:

1. Infrequent Episodic.

- 1.1. Associated with pericranial tenderness.
- 1.2. Not Associated with pericranial tenderness.

2. Frequent Episodic.

- 2.1. Associated with pericranial tenderness.
- 2.2 Not Associated with pericranial tenderness.

3. Chronic.

- 3.1 Associated with pericranial tenderness.
- 3.2 Not Associated with pericranial tenderness.

4. Probable.

- 4.1. Infrequent.
- 4.2. Frequent.
- 4.3. Chronic.

### EPIDEMIOLOGICAL DATA OF TENSION-TYPE HEADACHE

The prevalence of tension-type headache remains stable throughout the patient's life, reaching its maximum value of intensity in the 30s (1–3) for, from the age of 70, progressively reduce (4). It is more common in women than in men, with a ratio between 5:4 and 3:2 (5,6).

## PREVALENCE

Prevalence data for this type of headache are quite heterogeneous, varying between 20% and up to 70% depending on the clinical criteria used, the characteristics of the sample and the geographical area in which the data are collected or the year in which they are collected and which the studies are carried out.

Worldwide, data collected in primary care services indicate that the form of episodic tension-type headache affects more than 80% of the population at some point in life, and 10% of this population recurs frequently. For chronic tension headache, the data range around 2-3% in adult subjects (7).

In the latest edition of the International Classification of Headaches (ICHD-III), they point out that the data vary between 30% and 78%, they are the highest prevalence figures among all the types of headaches described (8) .

It seems that the prevalence of this type of headache is increasing in recent years (9). According to the Global Burden Disease of 2010, tension-type headache along with migraine appear as the second and third most prevalent dysfunction worldwide (10). North America in the first place and Europe in second, are the continents where this dysfunction is most detected (11).

## INCIDENCE

The incidence of tension-type headache considered as new-onset cases seems difficult to quantify. The data vary between 14 to 44 cases per 1000 people per year for tension-type headache (3,12).

## DATA IN SPAIN

In 2008, in a hospital in the province of Valladolid, the characteristics of the first 1,000 cases that attended consultations for headaches were analyzed. Following the ICHD-II criteria, 51.4% of cases were classified as migraine, 16% tension-type headache, 3.4% cranial neuralgia, and 2.4% trigeminal autonomic headache. The female/male ratio was 2.46/1. And the mean age was 43.19 years  $\pm$  17.1, coinciding with data from other population studies (13).

Another older study carried out in Aragón in 1995 analyzed the characteristics of the patients who attended the neurology service in the community, and of these, which presented headaches. During 3 months, 3,489 patients attended the neurology service, of which 25.5% requested consultation due to headaches. 42% diagnosed with migraines and 30.1% with chronic tension-type headache (14). If we compare the data of these two studies with others carried out in the general population, we can think that

it would be necessary to take into account that migraine is more frequent in specialty consultations while tension-type headache is considered more prevalent in the general population and in consultations of Primary Care.

### Socioeconomic effects

Tension headache can cause high levels of disability, not only to patients and their families, but also to society due to its high prevalence (11). In a study carried out in several European countries during the years 2008 and 2009, they calculated that the socioeconomic cost produced by patients with tension-type headache between 18 and 65 years old amounted to 21 billion euros, which corresponded to an average per patient of 303 euros per year. year (15).

### CLINICAL PRESENTATION

In addition to the common clinical features described in the definition, tension headache subtypes are mainly classified into chronic and episodic depending on how the frequency and duration of symptoms vary.

The most frequent common clinical findings in these patients are increased sensitivity to manual palpation in the pericranial myofascial structures. (16–19) and the increase in the tone of the muscles of the cervical, cranial and scapular region (20). The tone of the craniocervical-scapular muscles and local sensitivity are closely related, without presenting a correlation with the periods of headache. This suggests that this musculature remains constantly altered and is not dependent on episodes of pain (21). Another symptom that is frequently associated with tension headache is cervical pain, which appears in up to 88.4% of these patients (22).

On many occasions it is common to find myofascial structures with painful points on palpation (trigger points), decreased pressure pain threshold or postural alterations such as head thrust (20). Symptomatic alterations of the myofascial structures defined as active trigger points are prevalent in both adults and children in muscles such as the upper trapezius, the sternocleidomastoid or the temporal (23). For the suboccipital musculature, a typical area of referred pain is defined over the occipital and towards the temporal area, which is frequently perceived as bilateral headache. In patients with episodic tension-type headache, active trigger points have been found in 60% of cases, and in the remaining 40% they appeared in a latent state (24). In the upper trapezius, an increase in pain sensitivity has also been evidenced, both in the skin and in the muscle, compared to distal regions in the lower extremity for the same patients with chronic tension-type headache. (25).

## ETIOLOGY AND RISK FACTORS

Some of the risk factors that favor the development of tension-type headache have been described: low socioeconomic status, poor self-perceived health status, difficulty relaxing after work, frequent use of medications or sleeping few hours per night are associated with appearance and perpetuation of this type of headache (12,26).

## PATHOPHYSIOLOGY

The causal mechanisms of tension headache are not fully understood. Although it seems that in the frequent and infrequent episodic mode peripheral mechanisms may be more involved, in the chronic mode more central pain mechanisms are considered as the cause of the symptoms (8). Currently, despite having diagnostic criteria clearly defined by the ICHD, tension-type headache is not a perfectly defined entity in terms of its clinical and pathophysiological aspects.

Painful stimuli from sensitized pericranial tissues can cause referred pain to the head and be perceived as headache. Specifically, the myofascial trigger points of the muscles of the cervical and scapular area may be involved in the genesis of tension headache.

It seems that the dysfunction of peripheral mechanisms is more important in the type of episodic tension-type headache (27–29) and yet, the process of central sensitization in many cases is the mechanism that causes the headache to become chronic (30). This central sensitization process has been related both to nociceptive stimuli maintained over time (due to the release of algogenic substances that stimulate peripheral nociceptor zones) and to dysfunction of the descending inhibition system (28,29).

Some of these neurotransmitter and neuromodulator substances (nitric oxide, peptide related to the calcitonin gene, substance P...) are involved in the chronicity of pain in patients with tension headache (19). These algogenic substances that contribute to peripheral sensitization appear in in vivo analysis of active trigger points (those points whose pattern of referred pain is responsible for the patient's symptoms) and do not appear in latent trigger points or in control points (31).

All this information makes us think that alterations in the sensitive mechanisms of muscle, tendinous and fascial tissues of the cranial and cervico-scapular region may play an important role in the genesis of tension headache. But currently, the lack of knowledge of the pathophysiology of this headache affects the understanding of both the effectiveness of treatment techniques and the prevention of chronification.

## DIAGNOSIS

The diagnosis of this type of headache is made based on the patient's clinical history and examination. Generally, the medical specialist establishes the diagnosis following the ICHD-3 diagnostic criteria.

If a patient meets the clinical criteria for tension-type headache and has normal neurological examination results, further testing is usually not necessary.

Manual palpation of the pericranial musculature is a very valuable but rarely used examination. Sensitivity of these muscles to palpation is the most common abnormal finding in tension-type headache, although its absence does not rule out tension-type headache. In some cases, it is useful to perform an eye fundus in order to rule out the presence of papilledema or other anomalies that may indicate the presence of secondary headaches (32).

## TREATMENT

From primary care consultations, which constitute around 80% of the reference consultation points for these patients (33), the most used treatment is pharmacological, which usually consists of simple analgesics and NSAIDs for cases of episodic tension headache, also in some cases combinations of analgesics containing caffeine are prescribed. For cases of chronic tension headache, tricyclic antidepressants such as amitriptyline are sometimes prescribed (34,35).

Manual physiotherapy treatment and the use of acupuncture have shown beneficial effects for the relief of symptoms in patients with frequent tension-type headache despite the lack of solid evidence to support their use (35). The treatment techniques used in physiotherapy, both passive and active, have multiple physiological effects. Mainly, symptom relief in patients with headaches is explained by two mechanisms: reduction of sensitization of peripheral structures and activation of descending inhibitory pathways (28).

## DIACUTANEOUS FIBROLYSIS

Diacutaneous fibrolysis (DF) is a treatment method used in the field of physiotherapy that aims to relieve mechanical pain in the musculoskeletal system. For this, "hooks" are used that, applied to the skin, destroy adhesions and irritative interaponeurotic or myofascial corpuscles, improving the mobility of the myofascial tissue in relation to all the adjacent structures. The term diacutaneous means "against the skin", as opposed to the term percutaneous which implies passing through the skin.

For the A.E.F.D (Spanish Association of Diacutaneous Fibrolysis) DF is defined as "specific instrumental intervention to normalize function in the musculoskeletal system, after an accurate diagnosis and preserving the integrity of the skin".(36)

In the 1960s, the Swedish physiotherapist Kurt Ekman began the development of this technique (37), being later modified by the Belgians Jean Burnotte and Pierre Duby (38). The reputation of this method was given due to the success in the treatment of occipitalgia, epicondylitis and rebellious tendinitis of the Achilles tendon.

This method implies a painless way of working, based on a centripetal approach towards the most symptomatic point in the tissue that can be treated. This treatment involves three successive phases to reduce the aggressiveness of the technique: digital palpation, instrumental palpation and fibrolysis. Digital palpation aims to locate intermuscular septa and anatomical structures of interest, instrumental palpation allows precise detection of points where the connective tissue has poorer mobility or adhesions between adjacent tissues are suspected, and fibrolysis is performed by additional traction with the hook designed to improve those adhered fibers and improve mobility between muscle compartments.

Initially Ekman and Colombo pointed to a purely mechanical effect of the technique, through the destruction of these adhesions and irritating corpuscles (37,39) while its successors also observed a positive effect on post-traumatic edema and symptoms of neurological pathologies (38).

This technique allows treating the myofascial tissue with more specificity, precision and depth than most of the techniques used in manual therapy for the treatment of tension headache.

To date, only four indexed works have been found that study the effect of this technique. All of them do it by applying fibrolysis in regions of the extremities, obtaining beneficial results on the pain and mobility of the joints on which it is applied (40–43).

## PROJECT JUSTIFICATION

Tension-type headache is a very prevalent pathology in the general population that, despite the wide variety of treatment techniques available, in many patients presents persistent symptoms and a tendency to chronicity.

In my daily clinical experience with patients affected by tension headache, many of them state that DF is the technique that is achieving permanent benefits in the course of their symptoms. DF, by producing appreciable results from the first sessions, contributes not only to improving the patient's clinical situation, but also to increasing the results of the rest of the applied techniques and treatments.

The good clinical results of the DF, in this and in other pathologies, make it have a growing boom among physiotherapists, both nationally and internationally. However, the effectiveness of DF has not been proven in clinical trials on tension headache.

The aim of this clinical trial is to objectify the clinical improvements of these patients and to verify if DF really provides an additional advantage to the usual treatment of tension-type headache.

If its efficacy is confirmed, it would represent an advance in the treatment of patients affected by tension-type headache, a very prevalent and disabling pathology that, despite the multiple treatments available, continues to be a challenge for physiotherapists in daily clinical practice.

## HYPOTHESIS AND OBJECTIVES

### HYPOTHESIS

The diacutaneous fibrolysis technique on the myofascial structures of the cranio-cervical region in patients with tension-type headache produces a reduction in the frequency and intensity of pain and an improvement in the function of the cervical region, as well as in disability and quality of life, perceived by patients.

### OBJECTIVES

#### MAIN OBJECTIVE

To identify the clinical results produced by an intervention by means of diacutaneous fibrolysis on the musculature of the cervical spine in patients with tension-type headache.

#### SECONDARY OBJECTIVES

- To describe the clinical effects produced by a diacutaneous fibrolysis intervention on myofascial structures of the craniocervical region in different aspects of pain in patients with tension headache.
- To describe the clinical effects produced by an intervention by means of diacutaneous fibrolysis on myofascial structures of the cranio-cervical region in the joint and muscular function of the cervical region in patients with tension-type headache.

- To describe the clinical effects produced by a diacutaneous fibrolysis intervention on myofascial structures of the cranio-cervical region in the posture of patients with tension-type headache.
- To describe the clinical effects produced by a diacutaneous fibrolysis intervention on myofascial structures of the craniocervical region on disability in patients with tension headache.
- To describe the clinical effects produced by a diacutaneous fibrolysis intervention on myofascial structures of the cranio-cervical region on quality of life in patients with tension headache.
- To relate the aforementioned clinical effects with the clinical characteristics of patients with tension-type headache, with the aim of establishing clinical prediction rules for the diacutaneous fibrolysis technique in this subgroup of patients.

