## STUDY SAMPLE

### SAMPLE SIZE

The variable improvement in headache frequency has been chosen as a reference for calculating the sample size.

The calculation was made with the online program GRANMO 7.12 with the comparison menu between two independent means with a unilateral contrast and the following values: alpha risk 0.05; beta risk 0.20; to detect a difference equal to or greater than 3 units; a common standard deviation of 5 units; a ratio between the number of subjects between groups 1 and estimating a 15% loss to follow-up. The result is that 41 subjects per group are needed, as in this study there will be two groups, there are 82 subjects in total. Recruitment of this number of subjects is expected to be feasible.

The statistical data necessary to perform the calculation have been obtained from the study by Castien et al.(48) on the comparison of the application of manual therapy techniques versus usual medical treatment in patients with chronic tension-type headache, with an outpatient population in the Netherlands area.

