#### STATISTIC ANALYSIS

The statistical study will be carried out with the SPSS version 22.0 for Mac program. The confidence level established for the analysis of the results will be 95%. The person who will analyze the results will be blinded to the interventions assigned to each subject.

To achieve the objectives of the study, a descriptive study, a comparative study, a correlational and regression study of the collected data will be carried out.

For the descriptive analysis of the quantitative variables, the central tendency indices (mean and median) and the dispersion indices (standard deviation and the minimum and maximum values) will be used. For qualitative variables, a study of frequencies will be carried out to find out the absolute and relative frequencies, and the valid and cumulative percentages. In some cases, the mode central tendency measure will be extracted.

Prior to carrying out the comparative study between both groups, a study will be carried out to determine the normality and homoscedasticity of the study's scale variables and thus be able to use the corresponding statistical operations.

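### The secondary objective of establishing clinical prediction rules asks more than a trial sized for one 3-unit group difference can deliver, and should be restated as exploratory

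*Protocol*

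**What the plan says.** The protocol's Secondary Objectives list six aims. Five describe effects on pain, function, posture, disability and quality of life. The sixth relates those effects to patient characteristics, "with the aim of establishing clinical prediction rules for the diacutaneous fibrolysis technique in this subgroup of patients". Nothing there marks this aim as exploratory.

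Statistic Analysis says that, to meet the objectives, "a descriptive study, a comparative study, a correlational and regression study of the collected data will be carried out".

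Sample Size has a single basis: "The variable improvement in headache frequency has been chosen as a reference for calculating the sample size". Its result is "The result is that 41 subjects per group are needed, as in this study there will be two groups, there are 82 subjects in total".

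The table under Independent Variables lists 20 patient characteristics taken at history, several with more than two categories. Description of the Intervention adds baseline physical measures such as pressure pain threshold, cervical range of motion and ultrasound. The Dependent Variables table lists 14 outcomes. Only the intervention group receives the technique; controls lie supine for the same time.

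**The concern.** Two things do not fit the stated aim.

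The first is information. Searching many characteristics in a few dozen patients yields associations that look convincing in the data that produced them and predict poorly elsewhere.

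The second is the kind of evidence. A prediction rule for a technique has to identify patients in whom the technique does more than no treatment. A correlation between a characteristic and improvement does not show that. It mixes the effect of treatment with prognosis and with regression to the mean. Baseline headache frequency, for example, would be expected to correlate with improvement even if the technique did nothing. Separating these needs a treatment-by-characteristic interaction using both arms, and the trial is not sized for one.

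What is at stake is a named deliverable of the trial. If reported as an established rule, it would carry more authority than the data can give it.

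**Working it through.** **1. The plan's own sample size.** Sample Size gives a one-sided test at 0.05, power 0.80, equal groups, 15% dropout, and the effect and spread as "to detect a difference equal to or greater than 3 units; a common standard deviation of 5 units".

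- n per group = 2 × [5 × (1.645 + 0.842) / 3]² = 34.35.
- With 15% loss: 34.35 / 0.85 = 40.4, rounded up to 41. The stated figure reproduces.
- Expected completers: 41 × 0.85 = 34.85 per arm, about 35; 82 × 0.85 = 69.7, about 70 in total.

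**2. Patients per candidate.** Assumption: the 20 history variables are the candidates. Dummy coding of multi-category items and the added physical measures would raise the count; a short list would lower it.

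- Treated arm only: 35 / 20 = 1.75.
- Both arms: 70 / 20 = 3.5.

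**3. Chance findings if no candidate is related to outcome.**

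- At least one of 20 independent tests below 0.05: 1 − 0.95²⁰ = 0.64 for one outcome.
- Over all 14 outcomes: 20 × 14 = 280 tests, with 280 × 0.05 = 14 false positives expected.
- Expected apparent R² of a model with all 20 variables, p / (n − 1): 20 / 34 = 0.59 with 35 patients; 20 / 69 = 0.29 with 70.

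**4. If there is some real signal.** This was simulated with 20 independent candidates, two of them real, forward selection at p < 0.05 and 2,000 replicates. The true R² values are assumed, as the protocol gives none.

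| Patients | True R² | Share of selected predictors that are noise | Apparent R² | Out-of-sample R² |
|---|---|---|---|---|
| 35 | 0.10 | 67% | 0.23 | −0.21 |
| 35 | 0.25 | 46% | 0.36 | −0.06 |
| 35 | 0.50 | 35% | 0.59 | 0.33 |
| 70 | 0.25 | 36% | 0.32 | 0.13 |

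A negative out-of-sample value means that the rule predicts worse than the overall mean.

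**5. Interaction.** Take a characteristic that splits each arm 50:50, with SD 5 in every cell and 35 per arm, so 17.5 per cell.

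- SE of the interaction = 5 × √(4 / 17.5) = 2.39.
- Detectable with 80% power, two-sided 0.05: (1.960 + 0.842) × 2.39 = 6.7 units.
- At the protocol's one-sided 0.05: (1.645 + 0.842) × 2.39 = 5.9 units.
- Power if the effect differs by the full 3 units between subgroups: 24% two-sided, 35% one-sided.
- With no losses at all (41 per arm): SE = 5 × √(4 / 20.5) = 2.21, giving 6.2 units two-sided and 5.5 one-sided.

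**The case against.** The strongest reply is that the protocol does not describe the analysis that gives the worst figures. It speaks of a regression study of the collected data, which cover both arms. It does not confine the work to treated patients, enter all 20 variables in one model, or name those variables as the candidates. The 0.59 needs all of that; with both arms it is 0.29. It is also an unadjusted R² with no true association, and assuming no association is pessimistic for a list that includes baseline headache frequency, duration and intensity. This stands, and the figures are therefore given as conditional.

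A second reply is that short lists of predictors, interaction terms, shrinkage and validation are commonly left to a statistical analysis plan, which is not shown. That also stands, and their absence is not held against the protocol. What remains is the stated aim. An analysis plan can narrow the set of predictors, but it cannot add patients.

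A reader might infer that any resulting rule would be mostly noise, or false with near certainty. The documents do not support that. The share of noise depends on a true signal they do not give, and at a true R² of 0.50 some useful prediction remains. A reader might also infer that clinicians will use a rule to refuse treatment; no section plans such use.

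**Conclusion.** The point holds as a mismatch between a stated deliverable and the design. With about 35 completers per arm, a rule derived by correlation and regression is likely to be over-fitted and cannot be regarded as established. The firmest part does not depend on the number of candidates: even one pre-named, evenly split characteristic would have to change the effect by 6.7 units two-sided or 5.9 one-sided, about twice the 3-unit target, to be detected with 80% power.

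The conclusion rests on the protocol's SD of 5 and 15% loss. The per-candidate and false-positive figures rest in addition on taking the 20 history variables as the candidates and treating the tests as independent. The point concerns one secondary objective and leaves the main group comparison untouched. It should be corrected because it changes what the trial may claim.

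**What to change.** Reword the sixth secondary objective as exploratory and hypothesis-generating: to examine whether the effect of the technique differs by a small set of characteristics named in advance.

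Choose characteristics that will be recorded at baseline. Examples are headache frequency, muscle tenderness, and episodic or chronic diagnosis. Headache frequency is in the history table. Muscle tenderness appears only among the outcomes, so confirm that it is measured at the first assessment. The diagnosis is not a row in either variable table and would have to be carried over from the inclusion diagnosis.

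Estimate each as a treatment-by-characteristic interaction using both arms, and report it with a confidence interval. State that association with improvement in treated patients alone will not be read as predicting response to the technique, and that no prediction rule will be claimed as established without external validation.

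The cost is a change of wording, a less ambitious secondary objective, and interaction estimates that will be imprecise: with an SE of about 2.4 units, a 95% interval extends about 1.96 × 2.39 = 4.7 units either side. No extra patients are needed.
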